### Data management

Data will be stored in secure, password protected Australian cloud-based storage repositories (LabArchives and REDCap) [57]. Most participant information will have identifiers removed and be replaced by an individual code. Any necessarily identifiable participant information will be available to unblinded chief investigators only. Data will be embargoed from open sharing until the final publication of the primary outcomes paper.

### Protocol deviations

Deviations from this clinical trial protocol may occur and are permitted with rationale of patient safety and wellbeing or considered to be clinically appropriate. All protocol deviations will be recorded and reported to the Chief Principal Investigator or study committee.

### Adverse event reporting

Any untoward medical occurrence or clinical signs in participants or unintended disease or injury, related to the intervention procedures is considered an adverse event. The procedure for investigators reporting any adverse events involves; reporting the event via the electronic case report form (eCRF) through REDCap as soon as possible but no later than 10 working days for adverse events and 24 h for serious events. The adverse event information will be reviewed and approved by the investigator.

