### ‘Usual care’ control group

Routine dietetic care will be received by those participants randomised to the control group, also known as usual nutrition care. Usual care most commonly involves nurse-led malnutrition screening at each chemotherapy visit or acute inpatient admission, with patients at risk of malnutrition referred to a dietitian for nutrition assessment and intervention to optimise nutrition status. The timing and delivery of usual care will differ between health services.

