### Intervention group

The intervention will be provided in addition to usual care for a duration of six months. The intervention differs to usual care in terms of the mode, frequency and intensity of dietetic involvement. Dietitians will complete training in Behaviour Change Technique Taxonomy v1 (BCTT – V1) and all aspects of the intervention including symptom management, nutrition counselling, provision of oral nutrition supplement drinks, enteral nutrition regimen development and feeding tube management [30]. To reduce barriers to nutrition care, the nutrition intervention will be delivered via telehealth making it more widely accessible for a larger population, with the mode (telephone or videolink) determined by participant preference [21, 22]. Dietetic consultations will occur weekly at a minimum, as previous studies have displayed that consistent dietetic interactions can create a sense of support and rapport leading to greater engagement and disclosure of symptoms [21]. The intervention dietitian will contact participants as soon as practicable after randomisation to complete the initial nutrition assessment, and to arrange postage of a resource pack to participants. The pack contains an information booklet outlining key contacts, weight record templates, common side effects of treatment and how to manage them, and nutrition intervention strategies and education. The intervention dietitian will refer to the participant booklet during consultations, as a guide for dietary education and counselling. The booklet al.so outlines enteral feeding information including daily care of feeding tubes and a section to document individualised regimens for those that receive a tube. The participant can choose to record information in the booklet, such as medication changes or timing of symptoms, to report back to the intervention dietitian during weekly consults. Participants will also receive a diary to record PERT dosages, a PERT education booklet, and a pill box to store PERT capsules, as well as samples of oral nutrition supplement drinks to trial. Provision of trial supplement drinks will be tailored as required, depending on participants’ medical history e.g. participants with poorly controlled diabetes mellitus.

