#### Nutrition impact symptoms

All nutrition impact symptoms will be recorded for all intervention participants at each consult, and strategies to assist with the management of these will occur through goal setting, delivery of nutrition education and counselling, and recommended prescribed medications.

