#### Pharmacological support

To help manage nutrition impact symptoms in a timely manner, all participants will be provided with a standard set of prescriptions upon commencing the study which will be sourced by the site liaison, including prescriptions for PERT (25,000IU microsphere capsules), metoclopramide (10 mg tablets), and ondansetron (8 mg tablets or wafers). The intervention dietitian will be able to guide participants on correct usage as per medical instructions of the prescribed medications to assist in preventing or relieving symptoms. Severity of PEI and the requirement for PERT will be assessed using the American Gastroenterological Association Guidelines, which involves screening for presence of symptoms such as bloating, gas, altered bowel motions, weight loss and steatorrhea [38]. Timing, dosage and correct administration of PERT will be guided by the dietitian in line with oral intake (including oral nutrition supplement drinks), symptoms and/or supplemental enteral feeding and will be re-assessed at each telehealth consultation with dosages/timing adjusted as required. PERT will be administered either orally or with enteral feeds using either a naso-jejunal tube (NJT), percutaneous endoscopic gastro-jejunal tube (PEG-J) or radiologically inserted gastro-jejunal tube (RIG-J). If required, the intervention dietitian may recommend that participants purchase over the counter medications such as aperients or anti-diarrhoeals. All other medications will need to be prescribed by the participants’ treating medical team or general practitioner e.g. opioid analgesics or antidepressants, and will be charted accordingly. The intervention dietitian will work closely with the participant’s treating medical team to escalate the need for further medications as required.

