### Economic evaluation

Economic measures will be used to inform an economic evaluation, including both costs and measures of utility necessary to undertake a cost utility analysis. Health utility will be measured using the EQ-5D-5 L, which is a generic measure of health-related quality of life that does not include the cancer symptom-specific domains of the EORTC QLQ-C30 [43, 44]. However, use of a generic health utility scale is necessary for calculating the Quality-Adjusted Life Years (QALYs) lived necessary for conducting an economic evaluation consistent with welfare economics theorem. Other measures include; home care service provision (paid and unpaid) using the iMTA MCQ, direct health costs captured using Medicare Benefits Schedule (MBS) and Pharmaceutical Benefits Scheme (PBS) data, direct costs associated with hospital admissions, days spent in hospital, procedures performed in hospital, subjective reports on additional non-MBS health service use, e.g. private dietitian, and costs associated with feeding tube insertions and complications [53]. An incremental cost-utility analysis will be undertaken from the societal (primary), health service (secondary) and patient (secondary) perspectives. Costs will be valued at a 2024 base-year. QALYs lived will be calculated using an Australian utility value set for the EQ-5D-5 L [54]. Bootstrap resampling will be used to calculate a 95% confidence ellipse and cost-effectiveness acceptability curves.

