### Data safety and monitoring board (DSMB)

An independent multi-disciplinary and multi-site Data Safety and Monitoring Board (DSMB) will be convened to review accumulating trial data to monitor the safety and progress of the clinical trial. This will include reviewing data on recruitment progress, safety data including any adverse events, and protocol deviations. The DSMB will meet every 6 months for the duration of the trial, and will provide recommendations to the study Governance Committee, as needed.

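### An adverse event is defined as one related to the intervention procedures, so adverse event rates cannot be validly compared between arms

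*Protocol article*

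**What the plan says.** All references are to the protocol article.

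- **Adverse event reporting.** The defining sentence opens with "Any untoward medical occurrence or clinical signs in participants" and ends with "unintended disease or injury, related to the intervention procedures is considered an adverse event". The eCRF reporting rules and their time limits attach to events so defined. The section says that the investigator reviews and approves the event information. It does not describe causality as a separate assessment, and it names no class of event for occurrences that are not related.
- **‘Usual care’ control group.** "Routine dietetic care will be received by those participants randomised to the control group". No intervention procedure is described for this arm.
- **Intervention group.** "The intervention will be provided in addition to usual care for a duration of six months".
- **Nutrition impact symptoms.** "All nutrition impact symptoms will be recorded for all intervention participants at each consult". No matching record is described for controls.
- **Intervention fidelity and safety secondary outcomes.** The only harm item listed is feeding tube complications.
- **Data safety and monitoring board (DSMB).** The board reviews recruitment, protocol deviations and "safety data including any adverse events".
- **Economic evaluation.** The cost data include "direct costs associated with hospital admissions, days spent in hospital, procedures performed in hospital".

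**The concern.** A between-arm comparison of harms needs events counted by the same rule in both arms. Here the rule refers to a treatment that only one arm receives, so whether an event is counted depends on the arm and on an opinion about its cause.

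That matters in this population. Participants have borderline resectable, locally advanced or metastatic pancreatic cancer and are having chemotherapy. An infection, a vomiting episode or an admission can come from the tumour, the chemotherapy or the nutrition intervention, so attribution of a single case is weak evidence. Rates by arm are stronger evidence, because randomisation balances the background causes on average.

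At stake are two things: the DSMB's ability to set intervention-arm adverse events against a background rate, and the final report's ability to show either an excess or a reduction of such events under the intervention.

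**Working it through.** The point rests on a definition, so it is settled by setting the texts side by side. The document gives no adverse event rate to reproduce.

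**Step 1: what the qualifier governs.** The sentence can be read in two ways.

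- *Reading A:* relatedness qualifies the whole list (occurrence, sign, disease or injury). The comma before the qualifier favours this.
- *Reading B:* relatedness qualifies only the last items, disease or injury. But the opening words, "Any untoward medical occurrence or clinical signs in participants", already take in any disease or injury, related or not. Under this reading the qualifier changes nothing.

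Reading A is the one under which the qualifier has an effect, so it is the natural one. If sites split between A and B, they would record different things under one name, which is a further reason to repair the sentence.

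**Step 2: apply Reading A to each kind of event.**

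| Event | Meets the definition? |
|---|---|
| Intervention arm, judged related | Yes |
| Intervention arm, judged unrelated | No |
| Control arm | No, apart from the possible exception in Step 3 |

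**Step 3: possible exception.** Under Pharmacological support, "all participants will be provided with a standard set of prescriptions upon commencing the study". The sentence stands within the description of the intervention, so whether it reaches controls is unclear. If it does, a control participant could have an event tied to something the study supplied. A control count of exactly zero is therefore not established; a count on an unequal footing is.

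**Step 4: how much of the trial is affected.** The Power calculation section plans 41 per group, so 2 × 41 = 82 in total, and 41/82 = 50% of participants largely fall outside adverse event capture. The argument does not depend on the sample size.

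**Step 5: what can still be compared.**

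| Data | Section | Comparable by arm? |
|---|---|---|
| 12-month mortality | Data analysis (Cox regression) | Yes, stated |
| Hospital admission costs, days, procedures | Economic evaluation (incremental analysis) | Yes, an incremental analysis needs both arms |
| QLQ-C30 symptom scales (nausea and vomiting, pain, appetite loss, diarrhoea and others) | Primary outcome; Data collection | Yes, at three and six months |
| Weight, relative dose intensity | Secondary outcome measures | Yes, as trial outcomes |
| Recorded adverse events | Adverse event reporting | Not validly |

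The first four rows cover death, hospital use and several symptoms. They do not give rates by arm of specific events such as infection or aspiration. Hospital use is listed for the economic evaluation, and the document does not say that it goes to the DSMB.

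**The case against.** **The trial does compare harm between arms.** This stands. Mortality is compared explicitly, and hospital use, symptom scales, weight and dose intensity are planned outcomes. A reader might infer that no safety comparison is possible, or that a difference in admissions could not be shown. The document does not support either inference.

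**The DSMB is not confined to adverse events.** This also stands. Its remit is accumulating trial data and "safety data including any adverse events", and the word *including* leaves room for more. A reader might infer that the board would see data from one arm only; the text does not say so. It does not state a review by arm either.

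**The sentence can be parsed differently, and controls may receive study prescriptions.** This is enough to rule out saying that the control count is certainly zero. It does not rescue the definition, because the narrower parsing leaves the qualifier without effect.

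**The section does not say who judges relatedness, or whether that person is blinded.** Correct. A claim that unblinded staff filter the events would be inference. The point needs only that relatedness is a condition of entry.

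**A journal article condenses the protocol.** Grading scales, the collection window and the layout of safety tables may well be in the full protocol, and their absence here is no fault. The definition itself is stated, and a fuller document could change it only by contradicting it.

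**The trial is too small for adverse event rates to tell much.** Partly right. Take 41 per arm, 80% power, two-sided 0.05 and the arcsine approximation. The detectable difference on the arcsine scale is (1.960 + 0.842) × √(2/41) = 0.619. The control event rate is not in the document, so it is assumed over a range:

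| Assumed control rate | Rate needed in the other arm |
|---|---|
| 10% | 35% |
| 20% | 49% |
| 40% | 70% |

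Only large excesses would be detected formally. Recording both arms is still worthwhile as description and as the background rate for monitoring, but it would not make this a powered safety trial.

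**Conclusion.** The point holds in a limited form. As defined, adverse events are captured only when related to the intervention procedures, so adverse event rates cannot be validly compared between arms. On the natural reading, the gap covers essentially all control-arm events (41 of 82 planned participants) and any intervention-arm event judged unrelated. Comparisons of mortality, hospital use, symptoms, weight and dose intensity are not affected, and neither is the primary outcome.

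The conclusion assumes that the relatedness phrase governs the whole definition and that controls receive no intervention procedures. It does not depend on the control count being exactly zero, on who judges relatedness, or on any event rate. The definition should be corrected, but the flaw does not undermine the trial's main comparison.

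**What to change.** 1. Define an adverse event without reference to its cause.
2. In both arms, by the same method and over the same period, record at least serious events (deaths and unplanned admissions) and a short list of events named in advance. The mortality and hospital data already planned can supply much of this.
3. Record relatedness to the intervention as a separate eCRF field, completed after the event is entered.
4. Tabulate events by arm, for all events and for related events, for the DSMB and in the final report. Present the comparison as descriptive, given the sample size.

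The reporting timelines in the section can stay as they are.

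The cost is an eCRF change, an ethics amendment and modest added recording, mainly in the control arm, where weekly study contact is not planned. For the pre-named events, a source equally available in both arms should be used. Otherwise the weekly consultations would produce more recorded events in the intervention arm simply through closer observation.

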### Data safety and monitoring board (DSMB)

An independent multi-disciplinary and multi-site Data Safety and Monitoring Board (DSMB) will be convened to review accumulating trial data to monitor the safety and progress of the clinical trial. This will include reviewing data on recruitment progress, safety data including any adverse events, and protocol deviations. The DSMB will meet every 6 months for the duration of the trial, and will provide recommendations to the study Governance Committee, as needed.

### Ethics and trial registration

This study has undergone a full ethical review by the Human Research Ethics Committee at Monash Health and was approved on 30th of January 2024. Site-specific authorisation will be obtained from all sites prior to recruitment at each site. This trial was registered prospectively on the Australian New Zealand Clinical Trial Registry on 31st January 2024 (Trial ID: CTRN12624000084583).

### Confidentiality

All participant identifying documents will be disposed of appropriately after each participant interaction.

### Dissemination

The Governance Committee will review the trial findings once the study has ended, to assist with interpretation of study results. Study findings will be published in peer-reviewed journals and will be communicated through oral conference presentations to an audience of multidisciplinary health professionals, to inform researchers, health professionals and policymakers. Media outlets (both local and national) will be contacted once the findings are published, to increase exposure. Authors of international best-practice guidelines for management of people with pancreatic cancer will be contacted and provided with copies of our project report and manuscripts.

## Discussion

Malnutrition is commonly associated with pancreatic cancer [58]. Malnutrition, which involves the loss of skeletal muscle mass and function, reduction in immune function and can contribute to chemotherapy toxicity leads to poor outcomes such as QoL and shorter survival [6, 59]. To prevent malnutrition, nutritional intake must meet an individual’s nutrition requirements; this is challenging for people with pancreatic cancer due to the many tumour- and treatment-related impact on nutrient intake and absorption [60]. This study aims to appropriately manage nutrition impact symptoms and provide intensive nutrition support so that participants meet their nutritional needs, which may improve QoL.

Many studies have reported the detrimental consequences that treatment side effects and nutrition impact symptoms have on nutrition status [61, 62]. However, few studies have investigated the effect of dietitian-led interventions using a multidisciplinary approach to improve symptom management on QoL whilst also aiming to improve nutrition status [63]. Identification and management of nutrition impact symptoms are an important part of the dietetic nutrition care process, as symptoms impact heavily on nutritional intake [64]. This study will determine if aligning an intervention to focus on rapid management of nutrition impact symptoms as early as possible, may help to mitigate barriers to participants adhering to dietetic interventions, and thus improve nutrition status and QoL.

PEI is a common issue that impacts on nutritional intake with poor diagnosis and inadequate prescription of PERT by the medical profession [12]. Patients not prescribed PERT may experience a worsening of symptoms, impacting QoL and nutrition status through significant weight loss and malnutrition [65]. In a pilot study of 44 palliative patients with pancreatic cancer prescribed PERT, there was a significant reduction in diarrhoea, pancreatic and hepatic pain, bloating/gas within 1–3 weeks of its initiation [66]. In a large matched case control study, patients with pancreatic cancer who received PERT had a 262% greater adjusted median survival time (95% CI 2.27–3.02) compared to a pancreatic cancer control group who did not receive PERT (*n* = 807 per group) [11]. Dietitians are well placed to advise on PERT dosage and timing, given their expertise in management of gastrointestinal symptoms and understanding of an individual’s dietary patterns. Close guidance by a dietitian on dosage and timing of PERT in accordance with dietary patterns is recommended as the approach to managing PEI in all patients diagnosed with pancreatic cancer [66].

Despite active attempts to manage symptoms with the aim to improve oral intake, there are times when escalation to enteral nutrition along with symptom management may be needed to improve nutrition status. To our knowledge, there are limited published studies in this patient population exploring the effect of the combination of multiple nutrition interventions [67]. The use of enteral nutrition has been shown to be effective in head and neck cancer where oral nutrition is often impossible or very difficult [68, 69]. For patients with pancreatic cancer, oral nutrition may or may not be impacted by obstruction of the gastrointestinal tract; therefore it can become nearly impossible to meet nutritional needs orally, therefore an enteral feeding approach may be beneficial for some patients [3]. Benefits of a jejunal enteral feeding approach have been demonstrated in a recent feasibility study of 31 patients with inoperable pancreatic cancer who underwent surgical jejunal tube placement for supplementary feeding, resulting in improvement in QoL, gastrointestinal symptoms, lean body mass, and weight stability [67].

Intensive weekly monitoring of nutrition impact symptoms and nutrition status will provide information on the effect that consistent therapy has on outcomes such as QoL, survival and nutrition status. It will provide a comparison to usual dietetic care where nutrition interventions are often less consistent and less timely [7]. The use of telehealth as the mode of intervention delivery will allow more participants to engage regularly without contributing to time and cost burdens associated with travel and creates opportunities for participants living in regional areas to access early nutrition intervention to help improve health outcomes [23]. Understanding the effect of a comprehensive nutrition therapy intervention including effective symptom management, provision of oral nutrition supplement drinks, and supplemental enteral feeding, on QoL and health outcomes such as survival length will be enhanced through this study.

